### Investigational products

The vaccine to be used in this booster study is a licensed 17D YF vaccine, which forms part of the National EPI program of The Gambia, depending on product availability.

**
*Description of products*
**

This vaccine contains the Rockefeller17D-substrain 204 strain of Yellow fever virus. The exact potency of each batch is released with the certificate of analysis that accompanies each batch and potency is confirmed at the time of release. This vaccine is one of the YF vaccines previously used by the national EPI program.

**
*Formulation, packaging and labelling*
**

This vaccine is presented as a 1–10 dose vial with freeze-dried content which is reconstituted with a diluent, provided together with the vaccine by the manufacturer.

**
*Product storage and stability*
**

The vaccine is supplied with a Vaccine Vial Monitor which will be used to determine whether the vaccine is in a condition to be used at any point, including monitoring any temperature deviations.

**
*Dosage, preparation and administration of investigational products*
**

Reconstituted vaccines have to be kept in a vaccine carrier at 2–8°Celsius as per WHO and manufacturer requirements. Any remaining reconstituted vaccine not used has to be discarded after 6 hours. The standard dose is 0.5 ml and is administered subcutaneously in the deltoid region using standard vaccination syringes (needle size 25G × 3/4”) with a 45° injection angle.

**
*Concomitant vaccinations*
**

Children due additional EPI vaccines during their period of enrolment in the study will have them administered following the day 28 blood sample. These vaccines will either be administered by the study team or the study team will ensure the vaccines are given through the routine EPI clinic at the site. No vaccines will be administered concomitantly with the yellow fever vaccines.

### Selection and withdrawal of participants

**
*Selection of participants*
**

The study will recruit 750 healthy children to receive the booster dose of YF vaccine. A roughly equal number of boys and girls will be recruited. We do not expect there to be differences in the results by sex.

Participants will be recruited/ re-approached from the previously enrolled participants in each of the vaccine trials listed in
Table 1 below.

**Table 1. T1:** Cohorts to be re-approached as part of the trial.

Dates of 9-month yellow fever vaccination	Age in January 2022	Number of infants	Co-administered vaccines in original study	Serology in primary study	Study reference
Jul 2013 – May 2014	8 years 6 years	~1504	Combinations of IPV and measles and rubella	PRNT _50_	NCT01847872 SCC1327
Feb 2018 – Aug 2018	4 years	~675	Measles and rubella, OPV and PCV	PRNT _50_	NCT03197376 SCC1517
Dec 2020 – May 2022	9 months	~320	Measles and rubella, OPV and PCV	PRNT _50_	NCT03606096 SCC1600

Upon screening, potentially eligible children will continue until the end of study unless the trial is stopped for some reason. A child may be excluded from the trial for the purposes of vaccination and/or clinical sampling or if ongoing participation is considered to be against their best interests or if a contraindication to vaccination and/or to the obtaining of clinical samples is identified. Such decisions will be made by the PI in discussion with other members of the clinical trial team and/or the sponsor. A child excluded in this way would be replaced and hence this would not alter the target sample size of 750. If not enough children from the previous cohorts are available, we will aim to recruit appropriate age groups from community health centres. We expect this to be an exception rather than the rule.

**
*Eligibility of participants*
**

Participants must meet all of the inclusion criteria and none of the exclusion criteria to be eligible to participate in the trial. A representative sample of children will be recruited from the target population.

Inclusion criteria:

Any child fitting the required age cohorts who has a documented record of having received a primary dose of the Institut Pasteur YF 17D vaccine between 9 and 12 months of age. Documented evidence can be either a previous record of YF vaccination with dates in our own trial registers if the child was a previous participant or has documented evidence on its Infant Welfare Card.

Exclusion criteria:

Any child with a height/length for weight z-score of -3 or below.Any child known to be immunocompromised including any child with known vertical exposure to HIV infection.Any child with a history of serious adverse event or other contraindication to previous yellow fever vaccination.Participants who have an acute illness including abnormal vital signs or a fever of ≥ 37.5°C will not be vaccinated on the day but may be invited back for re-screening when they have recovered.Any child receiving immunosuppressive therapy.

**
*Concomitant medications*
**

Other than immunosuppressive drugs, no concomitant medication is excluded but will be noted in clinical files.

**
*Withdrawal of participants*
**

A study participant will be discontinued from participation in the study if:

Any clinical significant adverse event (AE), intercurrent illness, or other medical condition or situation occurs such that continued participation in the study would not be in the best interest of the participant.Development of any exclusion criteria.

Participants are free to withdraw from the study at any time without giving a reason.

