Solicited adverse events (AE) will be collected up to and including Day 3 following the booster vaccination. On Day 1, a member of the field team will conduct a home visit to assess and record any local or systemic AE including the presence of fever. Any child with a local or systemic response of concern will be reviewed by a study clinician the same day or within 24 hours according to the nature of the complaint. On Day 2 and 3 following vaccination, a member of the field team will contact the family by telephone to follow up on any ongoing or new local or systemic reaction. If there are any additional concerns, a home visit or clinic visit will be arranged as judged necessary by the study clinician. After Day 3 and until the end of the study, unsolicited adverse events will be collected. Parents will be asked to contact the study team to report any potential adverse events. These will be reviewed accordingly, and safety data recorded.

Immunology subgroups:

30 children per age cohort will be included in the immunology sub-studies which require a further blood sample on either Day 7 (+/-1) or Day 14 (+/-3) following the booster vaccination. For this purpose, the child will attend the clinic for blood sampling (see
Table 2).

**
*Final study visit*
**

On the final visit at Day 28 (+/-14), the child will be examined, and a further blood sample of 5–10 ml will be collected (5 ml for children under 5 years, up to 10 ml for older children).

**
*End of study*
**

The total duration of the clinical phase of the trial will be 12 months. This phase will end once up to 250 participants per age group have been enrolled and completed their D28 post booster vaccination visit. We will not substitute dropouts. The total duration of the trial is 18 months, and the trial will be considered as ended once the database has been cleaned and locked, the close out monitoring visit conducted and the end clinical study report submitted to MCA and to the IEC.

**
*Clinical evaluations*
**

During Visit 1 and Visit 2, clinical examination, vital signs, height and weight will be carried out and documented in the eCRF.

**
*Laboratory evaluations*
**

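### The only anthropometric exclusion criterion appears to transpose its index: read literally, it removes children who are heavy for their height and leaves in those who are severely wasted

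*Protocol article*

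**What the plan says.** In the Protocol article, Selection and withdrawal of participants, the first exclusion criterion is "Any child with a height/length for weight z-score of -3 or below". It is the only criterion based on body measurements. The article does not define the index or state its purpose, and nowhere gives it the other way round, as weight for height or length.

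The criterion is binding: "Participants must meet all of the inclusion criteria and none of the exclusion criteria to be eligible to participate in the trial". The same list is used again under Withdrawal of participants, where one ground for discontinuation is "Development of any exclusion criteria".

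The population is described in these words: "The study will recruit 750 healthy children to receive the booster dose of YF vaccine". The Introduction (Background) describes the vaccine as live-attenuated. The measurements needed to apply the rule are collected (Study procedures and evaluations, Clinical evaluations): "During Visit 1 and Visit 2, clinical examination, vital signs, height and weight will be carried out and documented in the eCRF".

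**The concern.** A z-score for one measurement given another places the child among children who share the second measurement. Height for weight therefore compares the child's height with that of children of the same weight. A score of -3 or below picks out a child who is extremely short for that weight. Severe wasting is the reverse pattern, low weight for the height, and on the written index it gives a high score that passes.

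A lower-tail cut-off at -3 on a height-and-weight index, in a trial of healthy children receiving a live vaccine, looks like a screen for severe wasting with the two terms transposed. If so, the line that decides entry, and can also decide discontinuation, points the wrong way. A site following it to the letter would turn away some heavy children and would not, by this rule, stop a severely wasted one. A site using the usual index would be departing from the written protocol. In either case text and practice need to be reconciled.

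**Working it through.** **Stated figure.** The plan attaches no number to this criterion, so there is nothing to reproduce. The check concerns direction.

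**Inputs.**
- Rule as written: height/length for weight, z-score of -3 or below (exclusion criteria).
- Correlation r between standardised height h and standardised weight w at a given age: not in the documents. Assumed, with a range of 0.5 to 0.9.
- Assumed joint distribution of h and w: bivariate normal.

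**Formulas.**
- Height-for-weight z: HWZ = (h - r·w)/√(1 - r²).
- Weight-for-height z: WHZ = (w - r·h)/√(1 - r²).
- Covariance of the numerators: r - r - r + r³ = -r(1 - r²). Dividing by (1 - r²) gives corr(HWZ, WHZ) = -r.

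The two indices are negatively correlated for any positive r, so the lower tail of one goes with the upper part of the other.

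**A child exactly at WHZ = -3.** Expected HWZ = (-r)(-3) = 3r, which is +1.5 at r = 0.5 and +2.7 at r = 0.9. Both are far above the -3 needed for exclusion.

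**Children with WHZ ≤ -3: chance of meeting the literal rule.** This is P(HWZ ≤ -3 and WHZ ≤ -3)/P(WHZ ≤ -3), from the bivariate normal distribution with correlation -r.

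**Children the literal rule does exclude.** Mean WHZ = r·φ(3)/Φ(-3), where φ(3)/Φ(-3) is about 3.28. The share with WHZ above 0 comes from the same bivariate normal distribution.

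| r (assumed) | P(meets literal rule, given WHZ ≤ -3) | P(WHZ > 0, given excluded) | Mean WHZ of excluded |
|---|---|---|---|
| 0.5 | 5.3 × 10⁻⁸ | 97.0% | +1.64 |
| 0.7 | 1.6 × 10⁻¹³ | 99.92% | +2.30 |
| 0.8 | 0 to computing precision | > 99.99% | +2.63 |
| 0.9 | 0 to computing precision | > 99.99% | +2.95 |

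Across the whole range the literal rule selects the opposite tail. The conclusion on direction needs only r > 0; the range affects only how sharp it is.

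**Does anything in Statistical considerations depend on this?** No. Wilson intervals with n = 250 match Table 3 to within 0.1 percentage point (the 50% row gives 43.8 to 56.2, against the printed 43.9 to 56.2). Power for 85% versus 75% is 80.0%. Power for a 15-point difference is 92.6% for 50% versus 65%, and 92.1% for 42.5% versus 57.5%. None of these calculations uses the anthropometric criterion.

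**The case against.** The strongest reply is that this is a slip of word order that no experienced team would act on. The -3 lower-tail cut-off signals what was meant, the trial runs at one site with vaccines given by the trial unit's own staff, and nothing shows that the literal reading was applied. This stands as a limit on the harm. It does not settle the text, because the criterion is binding and no other sentence corrects it.

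Nor is passing this one line the same as being admitted. Visit 1 includes history, physical examination, anthropometry and a final eligibility check. Acutely ill children are not vaccinated that day. The investigator, in discussion with the team or sponsor, may exclude a child "if ongoing participation is considered to be against their best interests or if a contraindication to vaccination" is identified. This also stands, although none of these is a measurement-based rule.

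A reader might infer three stronger points that the documents do not support:

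- **That severely wasted children were enrolled.** No enrolment data are shown, and no prevalence of wasting is given from which a number could be estimated.
- **That the criterion cannot be computed for the oldest cohort.** This depends on where an unnamed growth reference ends. A condensed article may leave the reference to the full protocol or to site procedures.
- **That the wording biases the comparison between age cohorts.** The same rule applies to all three cohorts, and no figure links nutritional state to post-booster titre. Baseline anthropometry is to be tabulated by cohort. Rationale for participant selection also foresees using anthropometric data from the earlier trials in considering confounding.

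**Conclusion.** The concern holds as a drafting error in a binding eligibility rule. As written, the criterion excludes children who are short for their weight, hence heavy for their height, and does not exclude severely wasted children. That does not fit the described population or the use of a live vaccine.

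The direction follows from the wording and from height and weight being positively correlated. The size of the mismatch rests on the assumed bivariate normal model with r from 0.5 to 0.9: practically no severely wasted child meets the literal rule, and about 97% or more of those it excludes are above average weight for height. That the intended index was weight for height or length is an inference from the cut-off, since the protocol states no purpose. The harm is conditional on literal application. Sample size, power and precision are unaffected.

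**What to change.** The sponsor should state which index was intended and which was actually applied at screening (apparently weight for height or length), and reconcile the protocol wording with it. The correction should carry through to the discontinuation ground that reuses the exclusion list.

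The article reports that recruitment and follow-up are complete, so rewording cannot change who was vaccinated. The intended index should therefore be recomputed from the Visit 1 height and weight in the eCRF, and any enrolled child who would have met the intended criterion should be reported descriptively. Such children should not be relabelled as protocol deviations merely because the text is corrected afterwards: the article defines a deviation as noncompliance with the protocol, and the corrected wording was not in force when they were enrolled.

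The cost is one line of text, a short recalculation on data already held, and possibly a few children to list. The choice of clinical threshold is left to the sponsor.

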### Study procedures and evaluations

For an overview, see the below Schedule of Events (
Table 2).

**Table 2. T2:** Schedule of Events.

Visit #	V1	Safety follow up visits	V1+7	V1+14	V2
Study Day	0	Visit 1 at home, visit 2&3 per phone unless concerns	7	14	28
Visit window (days)	-	Day 1–3 following vaccination	+1	+3	+14
Written informed consent	X				
Final eligibility confirmation	X				
History and physical examination	X				X
Vital signs & anthropometry	X		X	X	X
Blood sampling for YF serology and B cell memory	X				X
Study vaccine administration	X				
Solicited local and systemic AE data collection	X	X			
Unsolicited AE collection	X	X	X	X	X
T-cell responses (exploratory sub-study participants only)	X			X	
Transcriptome (RNA) (exploratory sub-study participants only)	X		X		
End of study visit					X

**
*Subject identification and sensitisation*
**

The databases of the previously conducted trials (summarized in
Table 1 above) will be accessed and interrogated for potentially available children according to age groups at the time of recruitment to the current booster study. Potentially suitable children according to the specified age cohorts will be identified and contact details for their families confirmed via mobile phone calls. During such calls, it will be confirmed that the family is happy to be contacted for a further MRC study. If willingness to engage is confirmed, the broad details of the booster study are explained to the carer, and the carer and child will either be invited to a sensitization visit at the clinical trial site or via a home visit to share the informed consent document. The family is then given an appointment to attend the clinical trials site for Visit 1.

**
*Enrolment visit (Visit 1)*
**

At Visit 1, the informed consent procedures will be completed, and the eligibility criteria will be confirmed. Vital signs and anthropomorphic data will be collected. The pre-booster blood sample will be collected and the booster dose of the YF vaccine administered as per protocol by the study team. The child will be observed in the clinic for 30 minutes. At the end of 30 minutes it will be confirmed by a nurse to the study clinician that the child remains well prior to them leaving clinic.

**
*Follow-up*
**

Solicited adverse events (AE) will be collected up to and including Day 3 following the booster vaccination. On Day 1, a member of the field team will conduct a home visit to assess and record any local or systemic AE including the presence of fever. Any child with a local or systemic response of concern will be reviewed by a study clinician the same day or within 24 hours according to the nature of the complaint. On Day 2 and 3 following vaccination, a member of the field team will contact the family by telephone to follow up on any ongoing or new local or systemic reaction. If there are any additional concerns, a home visit or clinic visit will be arranged as judged necessary by the study clinician. After Day 3 and until the end of the study, unsolicited adverse events will be collected. Parents will be asked to contact the study team to report any potential adverse events. These will be reviewed accordingly, and safety data recorded.

Immunology subgroups:

30 children per age cohort will be included in the immunology sub-studies which require a further blood sample on either Day 7 (+/-1) or Day 14 (+/-3) following the booster vaccination. For this purpose, the child will attend the clinic for blood sampling (see
Table 2).

**
*Final study visit*
**

On the final visit at Day 28 (+/-14), the child will be examined, and a further blood sample of 5–10 ml will be collected (5 ml for children under 5 years, up to 10 ml for older children).

**
*End of study*
**

The total duration of the clinical phase of the trial will be 12 months. This phase will end once up to 250 participants per age group have been enrolled and completed their D28 post booster vaccination visit. We will not substitute dropouts. The total duration of the trial is 18 months, and the trial will be considered as ended once the database has been cleaned and locked, the close out monitoring visit conducted and the end clinical study report submitted to MCA and to the IEC.

**
*Clinical evaluations*
**

During Visit 1 and Visit 2, clinical examination, vital signs, height and weight will be carried out and documented in the eCRF.

**
*Laboratory evaluations*
**

No routine clinical laboratory blood samples will be collected in this study. The research blood samples will be collected on V1 and V2 for YF serology and B cell memory responses for which PBMC will be isolated and stored. If, based on initial laboratory work, it is determined that a smaller number of PBMC will be required at this timepoint, serum will be collected alone.

30 children per age cohort will be included in the immunology sub-studies which require a further blood sample on either Day 7 (+/-1) or Day 14 (+/-3) following the booster vaccination. To this purpose, the child will attend the clinic for blood sampling.

At any timepoint, a maximum of 5 ml of blood will be collected from children younger than 5 years of age and up to 10 ml from older children.

Material Transfer agreements will be developed with any collaborating laboratories and valid certificates of accreditation will be provided for the external laboratory at the time of submitting the Material Transfer Agreement.

### Safety considerations

Yellow fever vaccines are generally exceptionally safe, and millions of doses have been given to adults and children worldwide. There have been rare reports of serious side-effects from the yellow fever vaccine. The rates for these severe ‘adverse events following immunization’ (AEFI), when the vaccine provokes an attack on the liver, the kidneys or on the nervous system are between 0 and 0.21 cases per 10 000 doses in regions where yellow fever is endemic, and from 0.09 to 0.4 cases per 10 000 doses in populations not exposed to the virus
^
1
^. The risk of AEFI is higher for people with primary or secondary immune deficiency who will therefore be excluded from this study. In addition, any child with a history of serious adverse event to the previous yellow fever vaccine would be excluded from the booster study.

**
*Adverse events*
**

An adverse event (AE) is any untoward medical occurrence in a study participant which does not necessarily have a causal relationship with either the vaccines administered or study participant. An AE therefore includes any unfavourable and unintended sign (including an abnormal laboratory finding), symptom, or disease occurring during the study period. Any AE which occurs after an immunization may be termed an AE following immunization (AEFI). For this trial, there will be active surveillance for local and/or systemic adverse events following immunization (AEFI) up to and including Day 3 following the booster vaccination (
Table 2A and
Table 2B).

Established criteria will be used to record such events:

**Table 2A. T2A:** Local solicited adverse events.

Local administration site	Grade 0	Grade 1 Mild	Grade 2 Moderate	Grade 3 Severe	Grade 4 § Potentially Life Threatening
Pain	No pain	Pain causing no or minimal limitation to use of limb	Pain causing greater than minimal limitation to use of limb	Pain causing inability to perform usual social and functional activities	Pain causing inability to perform basic self-care function or hospitalization indicated
Redness/Erythema ‡ (size as well as grade will be collected)	No redness/ erythema	≤ 2.5cm in diameter	> 2.5cm in diameter with < 50% of the surface area of the extremity segment involved (e.g. lower arm or thigh)	≥ 50% of the surface area of the extremity segment involved (e.g. lower arm or thigh) OR ulceration OR secondary infection OR phlebitis OR sterile abscess OR drainage	Potentially life- threatening consequences (e.g. abscess, exfoliative dermatitis, necrosis involving dermis or deeper tissues)
Swelling/induration ‡ (size as well as grade will be collected)	No swelling/ induration	≤ 2.5cm in diameter	> 2.5cm in diameter with < 50% of the surface area of the extremity segment involved (e.g. lower arm or thigh)	≥ 50% of the surface area of the extremity segment involved (e.g. lower arm or thigh) OR ulceration OR secondary infection OR phlebitis OR sterile abscess OR drainage	Potentially life- threatening consequences (e.g. abscess, exfoliative dermatitis, necrosis involving dermis or deeper tissues)

§ any AE resulting in death will be defined as grade 5 severity. ‡ grading based on the greatest single diameter or measured surface area. Based on the National Institute of Health, Division of AIDS (DAIDS) Table for Grading the Severity of Adult and Pediatric Adverse Events – Corrected Version 2.1 July 2017.

**Table 2B. T2B:** Systemic solicited adverse events.

Systemic	Grade 0	Grade 1 Mild	Grade 2 Moderate	Grade 3 Severe	Grade 4 § Potentially Life Threatening
Acute allergic reactions	No acute allergic reaction	Localized urticaria (wheals) with no intervention indicated	Localized urticaria (wheals) with intervention indicated OR mild angioedema with no intervention indicated	Generalized urticaria OR angioedema with intervention indicated OR symptoms of mild bronchospasm (wheeze)	Anaphylaxis OR life-threatening bronchospasm (wheeze) or laryngeal oedema (stridor)
Axillary Temperature	< 37.5°C	37.5 to 38.4°C	38.5 – 38.9°C	39.0 – 40.0°C	> 40°C
Vomiting	No vomiting	Transient or intermittent AND no or minimal interference with oral intake	Frequent episodes with no or mild dehydration – oral rehydration solution indicated	Persistent vomiting resulting in orthostatic hypotension OR aggressive rehydration indicated (e.g. intravenous fluids)	Life threatening consequences (e.g. hypotensive shock)
Diarrhoea	No diarrhoea	Liquid stools (less formed than usual) but usual number of stools	Liquid stools with increased number of stools OR mild dehydration	Liquid stool with moderate dehydration	Life threatening consequences (e.g. liquid stool resulting in severe dehydration, hypotensive shock)
Irritability	No irritability	Crying more than normal/irritability but no or minimal interference with usual social and functional activities	Crying more than normal/irritability causing greater than minimal interference with usual social and functional activities	Crying more than normal/irritability preventing usual social and functional activities	Requiring hospitalization due to irritability
Drowsiness	No drowsiness	Sleeping more than normal/drowsiness but no or minimal interference with usual social and functional activities	Sleeping more than normal/drowsiness causing greater than minimal interference with usual social and functional activities	Sleeping more than normal/drowsiness preventing usual social and functional activities	Requiring hospitalization due to drowsiness
Appetite	Eating/ feeding normally	Eating/feeding less than normal but no or minimal interference with usual social and functional activities	Eating/feeding less than normal with greater than minimal interference with usual social and functional activities	Eating/feeding less than normal preventing usual social and functional activities	Requiring hospitalization due to not eating/feeding.
Rash at a site other than product administration site	No rash	Localized rash at a site other than the product administration site.	Diffuse rash OR target lesions	Diffuse rash AND vesicles or limited number of bullae or superficial ulceration of mucous membranes at one site	Extensive of generalized bullous lesions OR ulceration of mucous membranes involving two or more distinct mucosal sites OR Stevens-Johnson syndrome OR toxic epidermal necrolysis.

§ any AE resulting in death will be defined as grade 5 severity. Modified from the National Institute of Health, Division of AIDS Table for grading the severity of adult and pediatric AE – Version 2.1 July 2017; US Department of Health and Human Services, Food and Drug Administration, Guidance for Industry, Toxicity Grading Scale for Healthy Adult and Adolescent Volunteers Enrolled in Preventative Vaccine Clinical Trials, Sep 2007.

**
*Serious adverse events (SAEs)*
**

An AE will be considered to be serious (i.e. SAE) if:

It results in death.Is life-threatening (an event where the participant was at risk of death at the time of the event).Requires in patient hospitalization or prolongations of existing hospitalization.Results in persistent or significant disability.

The start date for an SAE is defined as the day the relevant SAE criteria were met, not the day an AE which subsequently developed into an SAE began. The end date for an SAE is the day the final AE resolves, NOT the day the criteria rendering the AE serious resolves, i.e. if a participant is admitted with dehydration secondary to gastroenteritis, the SAE only ends when the diarrhoea resolves even if the infant has been discharged sometime before this. ‘Death’ and ‘Persistent or significant disability/incapacity’ will be defined as ongoing and will be closed for the purposes of further reporting once relevant clinical details have been captured (e.g. cause of death) and, in the case of disability/incapacity, if the condition is considered stable in the short term. 

**
*Reporting procedures*
**

SAEs will be reported by the PI to the sponsor and the local safety monitor within 24 hours of the investigator team becoming aware. The report should be submitted on the designated SAE reporting form for the trial. The reports will be submitted by e-mail or via the online reporting form-depending on MRCG SOPs. Follow-up reports will subsequently be submitted as new information becomes available until the SAE is closed or defined as ongoing.

Deaths occurring in the trial, irrespective of whether judged to be related or expected will be reported by the investigator by letter to the Gambia Government/MRCG joint ethics committee at their next meeting. SAEs that are judged to be related to investigational products and unexpected (SUSAR) will be reported by letter by the PI to The Gambia Government/MRCG Joint ethics committee within 24 hours.

SAEs that are judged to be related to investigational products but not unexpected will be reported by letter by the PI to The Gambia Government/MRCG Joint ethics committee within 15 calendar days or within 7 calendar days if the event is fatal or life threatening.

All SAEs will be reported by the PI to the Gambia Government/MRCG joint ethics committee in the annual report.

All deaths and all SAEs that are judged to be related to investigational products will be reported to the Republic of the Gambia MCA by the sponsor according to the latest requirements of the agency.

If new information becomes available that may alter the safety or conduct of the trial the investigator will inform the sponsor, the Local Safety Monitor, The Gambia Government/MRCG Joint Ethics Committee and The Gambia MCA in writing as soon as they become aware and generally within 5 calendar days.

**
*Safety oversight*
**

This trial uses an already licensed product that is in general use in The Gambia with an established safety record. The product has also been used in booster vaccinations. The trial is therefore considered to be relatively low risk. A DSMB will review safety data on a regular basis as per the DSMB charter. A local safety monitor is in place and will review local and systemic AEs and any SAEs, as will the trial management team on an ongoing basis.

